# Acceptability and feasibility of a community-based strength, balance, and Tai Chi rehabilitation program in improving physical function and balance of patients after total knee arthroplasty: study protocol for a pilot randomized controlled trial

**DOI:** 10.1186/s13063-021-05055-5

**Published:** 2021-02-11

**Keywords:** Total knee replacement, Falls, Tai Chi, Rehabilitation, Prevention, Multi-faceted intervention, Lower limb muscle strength, Balance, Coordination

## Abstract

**Background:**

The rate of falls in patients after total knee arthroplasty (TKA) is high and related to lower limb muscle weakness and poor balance control. However, since routine post-TKA rehabilitation is uncommon, it is paramount to explore alternative strategies to enhance balance and physical functioning in post-TKA patients. As Tai Chi is a proven strategy for improving balance in older people, the proposed study aims to determine the feasibility and acceptability of a 12-week community-based post-TKA multimodal Tai Chi program and to collect preliminary data with respect to the efficacy of such a program in improving balance and physical functioning in post-TKA patients as compared to usual postoperative care.

**Methods:**

A single-blinded 2-arm pilot randomized controlled trial will recruit 52 community-dwelling post-TKA patients (aged > 60 years) in Hong Kong. In addition, 26 untreated asymptomatic controls will be recruited for comparison purposes. The TKA patients will be randomized into either a 12-week multimodal Tai Chi rehabilitation group or a postoperative usual care group (26 each). Participants will perform the outcome assessments at baseline, 6, 12, 24, and 52 weeks after TKA, while asymptomatic controls will have the same assessments at baseline, 12, and 52 weeks after baseline. The rate of recruitment, retention, and attrition, as well as adherence to the intervention, will be measured and used to determine the feasibility of the study and whether a full-scale effectiveness trial is warranted. Further, qualitative interviews will be conducted to explore the acceptability and possible barriers to the implementation of the intervention. Primary and secondary outcomes including both patient-reported surveys and performance-based tests will be compared within and between groups.

**Discussion:**

The study will determine the feasibility and acceptability/potential efficacy of community-based rehabilitation for post-TKA patients and assess whether the intervention has the potential to be assessed in a future fully powered effectiveness trial. The findings will also be used to refine the study design and guide the conduction of a future definitive randomized controlled trial.

**Trial registration:**

ClinicalTrials.gov NCT03615638. Registered on 30 May 2018. https://clinicaltrials.gov/ct2/show/NCT03565380

**Supplementary Information:**

The online version contains supplementary material available at 10.1186/s13063-021-05055-5.

## Background

Total knee arthroplasty (TKA) is a well-established surgical intervention for patients with end-stage knee osteoarthritis (OA) to alleviate knee pain, correct knee deformity, and improve patients’ quality of life [1, 2]. However, research has consistently reported that the fall rate of post-TKA patients (up to 40%) is comparable to the pre-TKA fall rate (up to 50%) [3] and is higher than that of the age- and sex-matched asymptomatic controls [4, 5]. The persistent high fall rate may be partly ascribed to poor lower limb strength and the resection of soft tissues (e.g., the joint capsule) that contain numerous proprioceptors [6]. Such removal of proprioceptors may cause joint position sense deficits, increased muscle latency, and poor postural control [6]. Therefore, specific rehabilitation is needed to restore balance, movement control, and physical function of patients following TKA.

Recent evidence has shown that post-TKA, supervised progressive strength or balance training is better than inpatient care or home exercises in improving short- and long-term functional outcomes [6, 7]. Recent systematic reviews concluded that compared to standard postoperative care, supervised progressive postoperative lower limb strengthening exercises significantly improve knee flexion and extension range of motion, 6-min walk test (6MWT) distance, and timed up-and-go test (TUG) completion times [7, 8]. Similarly, post-TKA balance training (e.g., agility training) significantly improves balance and physical function of patients that reduces the risk of falls (as reflected from tests of stair climbing, functional reach, single leg stance, sit-to-stand ability, and the TUG) [7].

Unfortunately, routine postoperative outpatient physiotherapy or rehabilitation service is not always offered to patients after TKA, especially those in the sub-acute to chronic phases. Therefore, it is essential to explore alternative rehabilitation strategies to enhance lower limb muscular strength, improve balance, and reduce trip/fall incidences in patients following TKA. While conventional rehabilitation interventions comprising strengthening and dynamic exercises that have shown beneficial effects on pain and function after TKA [8, 9], community-based Tai Chi may provide an inexpensive, feasible, and effective option to enhance functional performance in post-TKA patients. Previous clinical trials have demonstrated beneficial effects of Tai Chi on lower limb muscle strength and balance in older people and stroke survivors in Hong Kong [10, 11]. One report has also shown that a 12-week Tai Chi program significantly improves pain, balance, physical functioning, quadriceps endurance, and femoral neck bone density in patients with knee OA as compared to untreated controls [12]. Additionally, a randomized controlled trial (RCT) involving 702 community-dwelling older adults in Australia [13] revealed that compared to untreated controls, 16 weeks of weekly community-based Tai Chi training significantly reduced falls (hazard ratio after 24 weeks = 0.67, 95% CI = 0.49–0.93) and improved five out of six balance measures. These findings highlight the efficacy of Tai Chi for fall prevention. Given the success of previous Tai Chi trials, it is plausible that community-based Tai Chi may improve balance, lower limb strength, and physical function in post-TKA patients.

Intervention programs comprising multiple components have been reported to be the most effective for improving a number of musculoskeletal and functional outcomes in older adults [14]. Numerous studies have evaluated individual components of post-TKA treatment and demonstrated the efficacy of the functional training including strengthening and balancing exercises [6, 9, 15], but there are few data on the effects of multimodal intervention programs that incorporate functional exercises with Tai Chi for post-TKA patients. The primary objective of this pilot study is to assess the feasibility of recruitment processes including the number of eligible participants and retention rates and to collect preliminary data to determine if a fully powered clinical trial is warranted.

The second objective is to determine the feasibility of a 12-week community-based post-TKA multimodal program and collect preliminary data with respect to the efficacy of the combination of different exercise components (i.e., including evidence-based strengthening and balancing exercises, and Tai Chi) in improving balance and physical functioning in post-TKA patients as compared to usual postoperative care. A third group of asymptomatic controls will be included to investigate whether the postoperative rehabilitation program can restore balance and mobility of TKA patients more akin to asymptomatic individuals. It is hypothesized that the multifaceted exercises is a feasible intervention for post-TKA patients, and those in the intervention group will demonstrate better physical function and balance control than patients receiving usual postoperative care.

## Methods

### Study design

This is a single-blinded 2-arm RCT. TKA participants will be randomized to either a 12-week community-based rehabilitation program starting at 12 weeks after TKA, or usual postoperative care without outpatient physiotherapy. A third group of asymptomatic controls will be recruited to provide comparisons at various time points (Fig. 1). A third group of asymptomatic controls will be recruited to investigate whether the postoperative rehabilitation program can restore balance and mobility of TKA patients to the levels found in asymptomatic individuals (Fig. 1). All post-TKA participants will undergo five clinical assessments: 1 week before TKA, and at 6, 12, 24, and 52 weeks after TKA. Two orthopedic surgeons will use a standard parapatellar approach. Two common prosthesis designs (posterior stabilized and medial pivot) will be used in TKA surgery. Previous research has reported no significant differences in self-reported and physical performance outcomes between these prostheses 12 months after TKA [16]. In addition, the untreated asymptomatic controls will be assessed at baseline, and 12 and 52 weeks from baseline. This study protocol has been approved by the Human Research Ethics Committees at The Hong Kong Polytechnic University (HSEARS20171225001) and the Institutional Review Boards of two hospitals (UW 18-452) and has been prospectively registered on clinicaltrials.gov (identifier number: NCT03615638). The protocol has been developed in accordance with Good Clinical Practice, Standard Protocol Items: Recommendation for Interventional Trials (SPIRIT) (see Additional file 1 SPIRIT 2013 checklist). The Human Research Ethics Committees review all study activities annually including ethical conduct, regulatory compliance, and recruitment and retention and can initiate an independent study audit at any time. The investigator team meets biweekly to discuss enrolment targets and treatment fidelity. The study coordinator is responsible for ensuring that data is complete and monitoring study progress including sufficient recruitment and retention. Adverse events across conditions will be reviewed annually; issues with intervention delivery and other unintended consequences of either intervention are discussed during regular supervision meetings. Significant protocol modifications will be approved by relevant Institutional Review Boards and will be reported to relevant parties (e.g., ClinicalTrials.gov) in a timely manner. All participants have the option of discontinuing their participation in the study at any time, and this is indicated in the consent forms. Adverse events will be reported immediately to the principal investigator, tracked, and responded to according to regulatory guidelines. There are no criteria for the modification of the study interventions. As harm from this type of study is rare, there are no provisions in place for ancillary, post-trial, or compensation for study-related harms.

**Fig. 1 Fig1:**
[figure not shown]
A flowchart of the single-blinded 2-arm randomized controlled trial and non-randomized asymptomatic control comparative study. The multimodal program will run once per week over 12 weeks

### Recruitment

Participants scheduled for TKA will be recruited from the osteoarthritis clinics of two hospitals in Hong Kong. It is anticipated that at least 10 TKA patients will be eligible for this study every month and the recruitment will take place over a 2-year period. A trained researcher will contact potential participants who are scheduled for TKA by phone to provide the required information regarding the current study (including objectives, eligibility criteria, and interventions). Those interested will be scheduled for an in-person visit to a physiotherapy department at one of the participating hospitals. A physiotherapist/trained research assistant will check the eligibility of the participant and assess cognitive function with the Mini-Mental State Examination [17], if this assessment has not been recently administered. After obtaining written consent, participants will undergo baseline assessments on the same day. Untreated asymptomatic controls will be recruited from community centers through posters and will undergo the same baseline assessments after obtaining informed consent by blinded physiotherapists/a trained research assistant at one of the two participating hospitals. The reasons for exclusion and for non-participation of eligible candidates will be documented in a screening log.

### Inclusion and exclusion criteria of participants

TKA participants will be eligible for this study if they are (1) aged 60 years or above, (2) planning to undergo primary TKA within 1 month, and (3) living independently in the community. People will be excluded if they are living in assisted living facilities, requiring nursing care, or planning to reside away from the hospital district within 1 year, or they have prior experience in practicing Tai Chi exercise for at least 3 months. Other exclusion criteria include the following: unstable medical conditions, fracture of lower limbs, malignancy in the last 5 years, lower limb prosthesis/amputation, congenital defect that is considered to cause the present complaint, systemic inflammatory and autoimmune diseases, previous osteotomy, neurological diseases (e.g., Parkinson’s disease, stroke), blindness, revision TKA, complications after primary TKA, and cognitive impairment as indicated by a Mini-Mental State Examination score < 19 [17]. Untreated asymptomatic controls will include a non-randomized cohort recruited using the same selection criteria with the exceptions that they must report no knee pain in the last 3 years, or have no history of TKA or total hip arthroplasty.

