**Subjective assessments**						
Sociodemographic characteristics	Age, sex, weight, height, dominant leg, marital status, number of people in the household, smoking habit, educational level, work status (number of working hours per week), occupation, alcohol/smoking status, history of trips/ falls, elevator landing or non-elevator landing flat	x				
Comorbidities	List of diseases: respiratory disease, hypertension, cardiovascular disease, eye problems, hallux valgus, previous hip or knee arthroplasty	x				
Pain	11-point numeric pain rating scale [28]	x	x	x	x	x
Physical function	Chinese version of Knee Injury and Osteoarthritis Outcome Score [29]	x	x	x	x	x
Depression	Chinese version geriatric depression scale [30]	x	x	x	x	x
Physical activity	Physical Activity Scale for the Elderly (Chinese version) [31]	x	x	x	x	x
Global impression of change in the intervention/ usual care	Self-perceived global changes				x	x
Fear of falling	Falls Efficacy Scale [32]	x	x	x	x	x

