## Statistical analysis

The data regarding the feasibility, acceptability, adverse events, intervention adherence, missing data rates and data completion rates will be summarized using descriptive statistics. The experience and perception of participants toward the RCT solicited from semi-structured interviews will be analyzed by framework analysis [39, 40].

To determine the feasibility of studying the proposed outcomes in a definitive trial, inferential analysis will be conducted at 95% confidence intervals, and the significance level will be set at 0.05. The effect size of each intervention outcome will also be estimated. Descriptive statistics will be used to summarize patient demographic data. Baseline demographic and clinical variables (such as BMI, medication, number of comorbidities) in the three groups will be compared using analyses of variance (ANOVAs) and Kruskal-Wallis tests for parametric and nonparametric data, respectively. Any baseline variables that show significant between-group differences will be used as covariates in subsequent between-group analyses of outcome measures. Separate two-way repeated measures analyses of covariate (ANCOVA) or ANOVA will be used to evaluate within- and between-group changes in various outcome measures at several follow-up time points (i.e., 6, 12, 24, and 52 weeks after TKA for TKA patients, and 12 and 24 weeks after baseline for asymptomatic controls) in the three groups. Statistical analyses will be conducted using SPSS version 21.0 (IBM Corporation, NY, USA). Following the intention-to-treat principle, between-group differences in primary and secondary continuous outcomes in all randomized participants at different time points will be analyzed. Per-protocol analysis will also be reported for all planned outcomes in participants who strictly followed the protocol.

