## Discussion

Total knee arthroplasty has been the most common surgery for treating patients with end-stage knee osteoarthritis since early 1980 [41]. Although multiple studies have shown that TKA improves patients’ pain and physical function [1, 2, 42], up to 60% of post-TKA patients experience falls within the first year after surgery [5, 43, 44]. Previous research has highlighted that patients at 1 year after TKA still display poor walking performance and balance compared with age- and sex-matched asymptomatic controls [16]. A recent systematic review has highlighted some modifiable risk factors (such as reduced knee range of motion and lower limb muscle weakness) that may increase the risk of falls in post-TKA patients [45]. While post-TKA comprehensive postoperative rehabilitation programs are recommended to restore balance and reverse other substantial physical deficits secondary to lower extremity muscle weakness and deconditioning [7, 45], current clinical practice includes little in the way of post-discharge interventions for TKA patients [46, 47]. Although supervised progressive strengthening or balance training can improve function and balance of patients with knee OA or TKA [6, 15], it may be difficult and costly to rehabilitate TKA patients in outpatient physiotherapy clinics for a prolonged period after discharge. While regular exercises can improve physical, psychological, and mental health of older people with and without TKA [30, 48], it may be difficult for patients with TKA to initiate regular exercises without proper guidance or community support. The high cost of outpatient rehabilitation services may deter older TKA patients from receiving postoperative rehabilitation. Community-based exercises such as Tai Chi may offer a feasible and affordable option for patients with TKA. Tai Chi can be learnt and practiced anywhere and anytime without the need for special clothing. More importantly, Tai Chi has demonstrated beneficial effects in reducing falls in patients with knee OA and stroke survivors [11, 49] and can improve lower limb muscle strength, balance, and physical function, which ultimately leads to improvements in balance and reduced risk of falling [12, 50]. To date, no studies have investigated the effects of community-based Tai Chi rehabilitation on balance and physical function in patients with TKA or intervention.

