While interventions with multi-components have shown a beneficial effect on physical function in community dwelling older adults, none has evaluated a multifaceted approach incorporating a community-based exercise for post-TKA. This pilot randomized controlled trial will therefore evaluate the feasibility of a 12-week postoperative multimodal rehabilitation program (including evidence-based strengthening and balancing exercises, and Tai Chi) in improving balance and function of patients with TKA. We hypothesize that post-TKA patients in the intervention group will have superior physical function and balance control than post-TKA patients in the usual care group. Further, we hypothesize balance of the intervention group participants will approach the observed performance of asymptomatic controls. Since Tai Chi is widely accepted by Chinese in Hong Kong, this community-based Tai Chi rehabilitation strategy is likely to be well received by many post-TKA patients if it is proven effective in improving physical function and balance of TKA patients. The results of this study will assist in identifying the requirements of a community-based multifaceted rehabilitation for TKA patients as a definitive clinical trial, which may lead to a paradigm shift in rehabilitating post-TKA patients. In addition, the findings of this study will be disseminated to researchers and the public through the study’s entry on ClinicalTrials.gov, through publication in peer-reviewed journals, and through presentation of the findings to the scientific community at scientific conferences.

A cost-effectiveness analysis will not be conducted in the current study. However, incorporating health economic evaluations alongside RCTs are increasingly common to evaluate the cost-effectiveness of novel interventions. Healthcare costs related to the use of healthcare (e.g., number of doctor visits, number of hospitalizations, informal care such as assistance with personal care and household tasks), the cost related to the physical exercise program (costs of instructor and equipment), and quality of life should be identified and taken together to investigate whether the proposed intervention is a cost-effective treatment option*.*

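### The benchmark comparison with unmatched asymptomatic controls adjusts for age and sex only if a weak baseline significance test triggers it

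*Protocol article*

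**What the plan says.** The Study design section gives the control group its purpose: to find out whether the programme can "restore balance and mobility of TKA patients to the levels found in asymptomatic individuals". The Background states the same aim in softer terms, and the Discussion turns it into a hypothesis: "we hypothesize balance of the intervention group participants will approach the observed performance of asymptomatic controls".

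On who the controls are, the Recruitment section says: "Untreated asymptomatic controls will be recruited from community centers through posters". The TKA patients come from hospital osteoarthritis clinics. The eligibility section adds: "Untreated asymptomatic controls will include a non-randomized cohort recruited using the same selection criteria", with exceptions for recent knee pain and for hip or knee replacement. The shared age criterion is "aged 60 years or above", with no upper limit and no restriction on sex. No matching, quota or stratification of controls is stated.

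The protocol describes the deficit to be closed against a tighter comparator. The Discussion says that patients one year after surgery "still display poor walking performance and balance compared with age- and sex-matched asymptomatic controls", and the Background describes the excess fall rate against age- and sex-matched people as well.

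Table 1 records "Age, sex, weight, height, dominant leg, marital status" and further items at baseline. The Statistical analysis section compares baseline variables across the three groups by ANOVA or Kruskal-Wallis and then applies this rule: "Any baseline variables that show significant between-group differences will be used as covariates in subsequent between-group analyses of outcome measures".

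**The concern.** Balance and walking are likely to vary with age and sex as well as with the state of the knee. If controls and patients differ in age or sex, the measured gap mixes the knee deficit with that difference. Younger controls would make patients look further from recovery than they are, and older controls would make them look closer.

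The protocol's protection is adjustment triggered by a significance test. Such a test measures whether an imbalance is large relative to sampling noise, not whether it matters for the outcome. With 26 people per group it can miss an imbalance large enough to shift the gap. For the two randomized arms, baseline differences are due to chance. For a volunteer cohort, a systematic difference is possible, so the decision to adjust should not hang on a test.

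**Working it through.** **The plan's own figures.** The Sample size section gives 26 per arm and 78 in total: 3 × 26 = 78, of whom 2 × 26 = 52 are randomized. These agree. No effect size, SD or margin stands behind them, so there is no power figure to reproduce.

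**Inputs.** From the protocol: 26 per group and a significance level of 0.05. Assumed, because the protocol gives no values: the age difference between the controls and both TKA arms, d, in SD units; the share of women; and the correlation r between age and balance.

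**Chance that the rule flags an age difference.** For group means 0, 0 and d, the one-way ANOVA noncentrality is λ = 26 × [2(d/3)² + (2d/3)²] = 26 × (2/3) × d². Power comes from the noncentral F distribution with 2 and 75 degrees of freedom.

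**Bias left in the gap.** The true intervention-control gap was set to zero. Unadjusted, the mean spurious gap is r × d. The rule (adjust for age only if the ANOVA is significant) and unconditional adjustment for age were each simulated with 10,000 trials per setting.

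| d (SD) | λ | Flagged | Unadjusted, r = 0.3 / 0.5 | Protocol's rule, r = 0.3 / 0.5 | Always adjusted |
|---|---|---|---|---|---|
| 0.3 | 1.56 | 18% | 0.09 / 0.15 | 0.06 / 0.09 | within 0.01 of zero |
| 0.5 | 4.33 | 43% | 0.15 / 0.25 | 0.06 / 0.10 | within 0.01 of zero |
| 0.8 | 11.09 | 84% | 0.24 / 0.40 | 0.02 / 0.04 | within 0.01 of zero |

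At d = 1.0 the rule flags 96%.

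The averages under the rule pool trials that were adjusted with trials that were not. At d = 0.5, the mean gap in the trials left unadjusted follows by division, taking the adjusted trials to average zero: 0.062 / (1 − 0.427) = 0.11 SD for r = 0.3, and 0.098 / (1 − 0.432) = 0.17 SD for r = 0.5.

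**Sex.** With 70%, 70% and 50% women, the mean share is 0.633. The chi-square noncentrality is 26 × [2(0.067)² + (0.133)²] / (0.633 × 0.367) = 2.99 on 2 degrees of freedom, so the imbalance is flagged 32% of the time. For 75% v 50% the figure is 49%, and for 70% v 60% it is 11%. ANOVA and Kruskal-Wallis, the only baseline tests named, are not the natural tests for a two-category variable, so it is unclear how the rule would be applied to sex. Kruskal-Wallis on sex coded 0/1 would come close to the chi-square test and so would be about as weak.

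**Precision for scale.** At 26 v 26 with no dropout, the 95% half-width in SD units is t(0.975, 50) × √(2/26) = 2.009 × 0.277 = 0.56. At d = 0.5, the average bias under the rule is 0.06/0.56 = 11% to 0.10/0.56 = 18% of that half-width.

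**The case against.** The strongest reply is that the protocol already has a safeguard. It compares baseline characteristics across all three groups and commits in advance to adjusting for those that differ. Age and sex are recorded. The groups also share the age floor, independent living, the cognitive cut-off, the medical and neurological exclusions and the exclusion of experienced Tai Chi practitioners. A large age difference would usually be caught. What slips through leaves an average bias well inside random error. The primary endpoint is feasibility and acceptability, and the control comparison does not touch the randomized one. A shift in the benchmark also moves the reference equally for both TKA arms, so which arm lies closer is affected far less than the size of the gap.

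Most of this stands, and it rules out several stronger readings that a reader might infer:

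- That the restoration question cannot be answered at all. The planned adjustment and the recorded age and sex contradict this.
- That nothing aligns the groups at recruitment. The shared eligibility criteria do so in part.
- That posters draw younger or more active volunteers. This is plausible, but the protocol does not say it, and the direction of any imbalance is unknown.
- That patients will be declared restored or not restored. The protocol sets no such threshold.

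What the reply does not remove is the conditional trigger. Shared criteria do not equalize age within an open-ended range from 60 upward, nor do they equalize sex. For moderate imbalances the rule fails to act more often than it acts.

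**Conclusion.** The point holds as a limited analysis weakness in an exploratory comparison. The benchmark group is not matched on age or sex, and adjustment for either depends on a test with low power at 26 per group: about 18%, 43% and 84% for assumed age differences of 0.3, 0.5 and 0.8 SD, and about 32% for an assumed 70% v 50% women.

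For a 0.5 SD age difference the expected bias in the patient-control gap is about 0.06 to 0.10 SD, which is modest beside the half-width of about 0.56 SD. These sizes rest on the assumed differences, on an age-balance correlation of 0.3 to 0.5, on a linear age effect and on complete follow-up. The simulation covered age only. The case for change is that unconditional adjustment brings the simulated age bias to about zero with data already collected. Unmeasured differences between volunteers and patients would remain under either approach.

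**What to change.** In the Statistical analysis section, replace the significance-triggered rule for comparisons with the controls by a statement such as: every comparison between a TKA group and the asymptomatic controls will include age (continuous) and sex as fixed covariates, irrespective of baseline test results; the adjusted gap will be reported with a 95% confidence interval and described as exploratory, and unmeasured differences between volunteers and patients will be acknowledged.

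The Trial status section has recruitment ending on 1 November 2020, so matching may come too late. If control places are still open, fill them to balance sex and broad age bands against the enrolled TKA patients. Keep the bands broad: three age bands by two sexes would leave only 26/6, or about 4, controls per cell.

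The cost is two degrees of freedom and, if places remain, slightly slower control recruitment because some volunteers are turned away. No additional participants or measurements are needed.

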### Sample size

No formal sample size calculation was performed for this feasibility study. However, a minimum sample size for a pilot study to evaluate the feasibility of conducting a full-scale trial is suggested to be 50 per study [18, 19]. A total of 78 patients (26 per arm) were deemed an appropriate sample size for this trial to estimate the recruitment and retention rates and explore the acceptability of the intervention.

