## Endpoints and outcome measures

### Primary endpoint

The primary endpoint is to assess the feasibility and acceptability of trial design and procedures, including the recruitment and retention rates and identifying barriers to participation. This will inform the choice of the primary outcome for a full-scale trial and provide an estimation of the attrition rate for a sample-size calculation. The following will be measured and used to inform study feasibility:

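### The eligibility rule for asymptomatic controls joins its two conditions with *or*; read literally it admits people with knee pain or a joint replacement, probably a slip for *and*

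*Protocol article*

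**What the plan says.** The controls are defined in a single sentence of the protocol article, under Inclusion and exclusion criteria of participants. It begins "Untreated asymptomatic controls will include a non-randomized cohort recruited using the same selection criteria with the exceptions that" and continues "they must report no knee pain in the last 3 years, or have no history of TKA or total hip arthroplasty". No other section restates or corrects this rule.

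The Abstract says that "26 untreated asymptomatic controls will be recruited for comparison purposes". The purpose is given three times:

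- Background: the group serves to investigate "whether the postoperative rehabilitation program can restore balance and mobility of TKA patients more akin to asymptomatic individuals".
- Study design: the question is whether the program "can restore balance and mobility of TKA patients to the levels found in asymptomatic individuals".
- Discussion: "we hypothesize balance of the intervention group participants will approach the observed performance of asymptomatic controls".

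The primary endpoint is separate from this: "The primary endpoint is to assess the feasibility and acceptability of trial design and procedures".

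**The concern.** The group is useful only if its members are what the label says. The rule that decides membership is worded so that one of two conditions suffices, and each condition alone lets in people whom the label excludes: those with a painful knee, or those with an artificial knee or hip.

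What is at stake is the meaning of the patient-versus-control comparison. If such people were enrolled and have poorer balance or mobility, the reference level would drop. A smaller gap between the intervention group and the controls would then partly reflect who the controls were. Controls come from community centers by poster and must be at least 60, so the written rule is the main safeguard on the composition of the group.

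**Working it through.** **1. The plan's own figures.** Three groups of 26 give 3 × 26 = 78, which agrees with "A total of 78 patients (26 per arm) were deemed an appropriate sample size for this trial". Two TKA arms give 2 × 26 = 52, as in the Abstract. The article reports no formal sample size calculation, so there is no power figure to reproduce. Correcting the rule leaves these targets unchanged.

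**2. The rule as a truth table.**

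| Knee pain within 3 years | Knee or hip replacement | Eligible under *or* | Eligible under *and* |
|---|---|---|---|
| No | No | Yes | Yes |
| No | Yes | Yes | No |
| Yes | No | Yes | No |
| Yes | Yes | No | No |

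The literal rule admits 3 of 4 combinations. Requiring both admits 1 of 4.

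**3. Do the shared exclusions close the gap?** None of the listed exclusions removes a person for knee pain. The exclusion for a lower limb prosthesis or amputation might be read as covering joint replacement. Against that reading, Table 1 records earlier hip or knee arthroplasty as a baseline comorbidity, and a separate arthroplasty condition for controls would be redundant. Even if that reading is accepted, only the second row of the table drops out. The person with knee pain and no replacement still qualifies, so 2 of 4 combinations remain.

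**4. Possible effect on the benchmark.** Let f be the share of controls with knee pain and d their deficit in standard deviations (SD). The control mean then falls by f × d. Neither input is in the article, so the values below are assumptions that show only how the result depends on them.

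| f | d = 0.3 | d = 0.5 | d = 0.8 |
|---|---|---|---|
| 0 | 0 | 0 | 0 |
| 0.10 | 0.03 | 0.05 | 0.08 |
| 0.25 | 0.075 | 0.125 | 0.20 |
| 0.50 | 0.15 | 0.25 | 0.40 |

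**5. Scale for comparison.** With 26 per group and a common SD, the approximate 95% half-width of a difference in means is 1.96 × √(2/26) = 1.96 × 0.277 = 0.54 SD. Every entry in the table lies inside that margin. A shift of this kind would be systematic, though, and averaging more participants would not remove it.

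**The case against.** The strongest reply is that this is a drafting slip and nothing more. The group is called asymptomatic throughout, including in the disputed sentence, and few recruiters would enroll someone with a painful knee under that name. If both conditions were applied in practice, the effect is nil. That stands as the likely reading. It does not remove the need to correct an eligibility rule that says something else.

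A reader might infer that the benchmark is in fact biased, or that any bias must favor a finding of restored function. The article supports neither. It does not show that anyone with knee pain or a replacement was enrolled. The direction depends on such people performing worse, which is plausible but not shown, least of all for a pain-free person with an old replacement.

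A reader might also infer that controls must be awaiting TKA, because they share the patients' selection criteria. That criterion is listed for TKA participants, and the controls are untreated and followed from baseline, so the inference does not hold.

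Two further points limit the concern. First, controls undergo the same baseline assessments, and Table 1 includes a pain rating and arthroplasty history, so current pain and past replacement should be visible in the data. A baseline pain score cannot establish three pain-free years, however. Second, the comparison is secondary and non-randomized, in a pilot not powered for efficacy, with no margin set for calling function restored.

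It would go slightly too far to say that the randomized contrast cannot be touched. Under Statistical analysis, baseline variables are compared across all three groups, and those that differ significantly become covariates in later between-group analyses. The make-up of the control group could therefore influence the choice of covariates. This is an indirect route, and nothing in the article shows that it matters here.

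**Conclusion.** The point holds as a defect in the wording of an eligibility rule. The only operational definition of the controls, taken literally, is inconsistent with their label and with their use as a benchmark in the Background, Study design and Discussion sections. This rests on the text alone and is certain.

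Any distortion of results is conditional on two things: that the rule was applied as written, and that those it let in perform worse. Its size cannot be estimated from the article. It is zero if both conditions were applied, and the non-zero entries above come only from assumed inputs. The comparison mainly affected is the non-randomized one against controls. The feasibility and acceptability endpoint does not use it. The correction is worth making because a reader cannot tell from the text how controls were screened, and because the remedy is cheap.

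**What to change.** Rewrite the sentence so that a control must meet both conditions: three years without knee pain, *and* no previous TKA or total hip arthroplasty.

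Trial status gives 1 November 2020 as the end of recruitment, so a text correction alone is not enough. Check every enrolled control against the corrected rule, using the screening records together with the baseline pain rating and arthroplasty history. The screening log as described covers exclusions and refusals. If the three-year answer was not kept for enrolled controls, it would have to be asked for. State in the report how the rule was applied, and present the three-group comparison without any control who fails it.

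The cost is one changed word and a check of at most 26 records. The downside is that a few controls may be set aside, which makes an already small comparison somewhat less precise.
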